### Endpoints

The primary end-point of the study will be a reduction in left ventricular mass after 40 weeks of treatment. Left ventricular mass is a powerful predictor of cardiovascular and all-cause mortality in the general population[39] and in CKD [40]. A therapeutic reduction in left ventricular mass has been shown to effectively reduce cardiovascular morbidity and mortality [41,42]. Secondary end points are: i) change in aortic compliance measured by CMR; ii) change in arterial stiffness as assessed using pulse wave velocity and pulse wave analysis; iii) change in arterial elastance measured by echocardiography; iv) change in left ventricular systolic and diastolic elastance measured by echocardiography; v) change in left ventricular function as assessed by tissue Doppler imaging, strain and strain rate analysis and measurement of torsion; and vi) change in bone density on DEXA scanning and/or magnetic resonance imaging.

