**Figure 1 F1:**
[figure not shown]
**Study timeline**. 120 subjects will undergo baseline investigations before entering a 4 week open-label run-in phase in which all subjects will receive 1600 mg of sevelamer carbonate with meals. Participants will then be randomised to continue treatment with sevelamer carbonate 1600 mg with meals or identical placebo for the remaining 36 weeks. Safety monitoring will be performed every four weeks. Investigations will be repeated at week 40 after which subjects will have completed participation in the study.

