### Run-in Phase

Following baseline studies all subjects will receive 1600 mg of sevelamer carbonate with meals for 4 weeks during an open-label run-in phase (Figure 1) to assess tolerability, efficacy, compliance and side effect profile. The development of new symptoms that may relate to treatment and compliance with medication will be assessed at 2-weekly intervals during run-in. Serum phosphate will also be measured at 2-weekly intervals. In the event that serum phosphate falls below 0.8 mmol/L, the dose of sevelamer will be halved to 800 mg with meals (Table 2) and levels rechecked to ensure serum phosphate is >0.8 mmol/L. If serum phosphate remains below this level after 6 weeks and/or a dose reduction subjects will be withdrawn from the study after a final set of measurements.

**Table 2 T2:** Management of serum phosphate levels during open-label run-in phase

	Serum Phosphate (mmol/L)	Action
Week 2	<0.8	Reduce dose to 800 mg tds and continue to week 4
	>0.8	Continue to week 4

Week 4	<0.8	Reduce dose to 800 mg tds and continue to week 6 If already on 800 mg tds withdraw from study after week 4 visit
	>0.8	Randomise

Week 6	<0.8	Final measurements and withdraw from study
	>0.8	Randomise

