### Randomisation and Treatment Phase

At the end of the open-label run-in phase subjects will attend for a second study visit and the following will be repeated: i) office brachial blood pressure and heart rate measurement in triplicate; ii) applanation tonometry to determine aortic pulse wave velocity; iii) applanation tonometry to derive central pressure waveforms from pulse wave analysis; iv) collection of serum and plasma for haematological and biochemical analysis; v) storage of serum and plasma at -80°C for future assay of biomarkers associated with cardiovascular function and calcification; vi) collection of a spot urine sample to determine albumin: creatinine ratio; and vii) 24-hour urine collection for determination of phosphate excretion.

Participants will then be randomised by computer assignment to continue 1600 mg (or half-dose) sevelamer with meals or receive an identical placebo for the remaining 36 weeks (Figure 1). During this blinded treatment phase subjects will undergo monitoring of renal function and serum calcium, phosphate and PTH every four weeks. Serum phosphate levels will be managed according to a pre-defined protocol during the treatment period (Table 3). All measurements performed at the initial main study visit (except for the plain lateral abdominal radiograph) will be repeated at a final visit 40 weeks after baseline studies, marking the end of subject participation in the study.

**Table 3 T3:** Management of serum phosphate levels during treatment phase

	Serum Phosphate (mmol/L)	Action
At visit	<0.8	Recheck serum phosphate within 1 week
	>0.8	Continue routine 4-weekly checks

Within 1 week of visit	<0.8	Reduce treatment/placebo dose to 800 mg tds and recheck in 2 weeks
	>0.8	Continue routine 4-weekly checks

2 weeks after visit	<0.8	Final measurements and withdraw from study
	>0.8	Continue routine 4-weekly checks

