### Planned Statistical Analysis

Comparisons will be performed between the groups at baseline and after the 36-week treatment phase. The normality of distribution of all continuous variables will be determined using a normality plot and the Kolmogorov-Smirnov test. Normally distributed variables will be analysed using unpaired t-tests, χ^2 ^or repeated measures analysis of variance with corrections made for multiple comparisons. Variables not normally distributed will be log transformed prior to analysis to achieve normal distribution or, if this is not achieved, analysed by Mann-Whitney U or Kruskal-Wallis tests. Multiple linear regression models will be derived for left ventricular mass and measures of vascular and cardiac stiffness using stepwise regression analysis. Analysis will be by intention-to-treat. A p-value of <0.05 will be considered statistically significant.

Sample size calculations were based on the primary endpoint of change in left ventricular mass after 40 weeks of treatment. A previous study by our group evaluating the cardiovascular effects of spironolactone in patients with early CKD revealed a 14 g drop in left ventricular mass from baseline following 40 weeks of therapy [38]. Using data from this previous study, 55 subjects in each arm will provide at least 80% power of detecting an 8 g difference between the change in left ventricular mass from baseline to 40 weeks using a two-tailed t-test at the 5% significance level given a standard deviation of 15 g in the change in left ventricular mass from baseline. Recruiting 60 subjects to each group will allow a 10% withdrawal or dropout rate.

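### The primary endpoint is labelled as 40 weeks of treatment, but the randomised contrast is 36 weeks of continuing versus stopping sevelamer after a shared run-in, and a week-6 randomisation cannot meet both stated durations

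*Protocol article*

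**What the plan says.** The Endpoints section defines the primary endpoint without a comparator: "The primary end-point of the study will be a reduction in left ventricular mass after 40 weeks of treatment". The sample-size paragraph under Planned Statistical Analysis uses the same duration: "Sample size calculations were based on the primary endpoint of change in left ventricular mass after 40 weeks of treatment".

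The design sections describe a different contrast. Run-in Phase: "Following baseline studies all subjects will receive 1600 mg of sevelamer carbonate with meals for 4 weeks during an open-label run-in phase". The legend to Figure 1 continues: "Participants will then be randomised to continue treatment with sevelamer carbonate 1600 mg with meals or identical placebo for the remaining 36 weeks". The analysis paragraph also uses the shorter period: "Comparisons will be performed between the groups at baseline and after the 36-week treatment phase".

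On the schedule, Randomisation and Treatment Phase has participants continue sevelamer or "receive an identical placebo for the remaining 36 weeks", and says that the baseline measurements "will be repeated at a final visit 40 weeks after baseline studies". For a participant whose phosphate is below 0.8 mmol/L at week 4 while still on the full dose, Table 2 says "Reduce dose to 800 mg tds and continue to week 6". That participant is randomised at week 6 if phosphate is then above the threshold.

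**The concern.** An endpoint should say which comparison it rests on. Read literally, a reduction after 40 weeks of treatment describes a change within the sevelamer arm, since only that arm receives the drug for 40 weeks. The placebo arm takes sevelamer for at least its first 4 weeks, and that exposure falls inside its change from baseline.

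What is at stake is the claim the trial can support. The Summary section would read a positive result as evidence about phosphate lowering in stage 3 CKD in general. The design supports something narrower: the effect of continuing rather than stopping, among people who came through a run-in that assesses tolerability and compliance and requires phosphate above 0.8 mmol/L.

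The schedule conflict matters because the final visit carries the primary measurement. For a week-6 randomisation, the text does not say when that visit takes place.

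**Working it through.** **Which period the measurement covers, and which period is randomised**

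- Baseline Studies places cardiac magnetic resonance imaging and echocardiography before the run-in.
- The measurements repeated at the randomisation visit are blood pressure, pulse wave velocity, pulse wave analysis, blood and urine. Neither imaging method is listed, so change from randomisation cannot be calculated for left ventricular mass.
- Apart from final measurements on withdrawal, the next assessment is the final visit.

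| | Weeks 0 to 4 | Weeks 4 to 40 |
|---|---|---|
| Sevelamer arm | open-label sevelamer | blinded sevelamer |
| Placebo arm | open-label sevelamer | blinded placebo |
| Do the arms differ? | no | yes |

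The change score spans 40 weeks. The arms differ for 40 − 4 = 36 of them, and 4/40 = 10% of the interval is shared active exposure.

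**Timeline**

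- Randomised at week 4: 4 + 36 = 40. Both stated durations hold.
- Randomised at week 6 with 36 blinded weeks: 6 + 36 = 42, so the final visit is not at week 40.
- Randomised at week 6 with the final visit at week 40: 40 − 6 = 34, so there are not 36 blinded weeks.

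No reading satisfies both statements for a week-6 randomisation.

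**The plan's power figure**

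Inputs, all from Planned Statistical Analysis: 55 per arm, difference 8 g, SD of change 15 g, two-sided 5% t-test.

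- Standardised difference: 8/15 = 0.533.
- Normal approximation: 0.533 × √(55/2) − 1.96 = 2.797 − 1.96 = 0.837, giving power of 79.9%.
- Noncentral t: 79.2%.
- Required for 80%: 56 per arm (normal) or 57 (t).

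The stated 80% is essentially reproduced. The plan describes the 8 g as the difference between arms in change from baseline to 40 weeks. That is the quantity this design observes, with the shared run-in inside it, so the figure needs no discount for the run-in.

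**How many are affected at week 6**

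The protocol gives no number. Entry excludes phosphate below 0.8 mmol/L. Subject Withdrawal cites 1.2 ± 0.2 mmol/L from an earlier study in stage 3 CKD, so the threshold lies (1.2 − 0.8)/0.2 = 2 SD below that mean. This does not describe levels during the run-in on sevelamer, so it gives only a rough indication that such randomisations will be few.

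**The case against.** The strongest reply is that nothing is hidden. The abstract, Figure 1 and the design sections all describe the 4-week run-in and the 36 randomised weeks. The analysis paragraph compares the groups, and the powered quantity is a difference between arms. Forty weeks is also literally true of the sevelamer arm. All of this stands: the randomised comparison is valid, and selecting run-in completers is an openly stated design feature. What remains is that the primary endpoint, the one sentence a results paper will repeat, names neither the comparator nor the randomised duration.

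A reader might infer two stronger points that the protocol does not support.

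- **That power falls.** Scaling 8 g by 36/40 gives 7.2 g and about 70% power at 55 per arm by t-test. This assumes that the 8 g belongs to a full 40-week contrast, that the effect builds linearly, and that the placebo arm's early effect persists completely after stopping. The protocol states none of these. If the early effect washed out, the difference would return towards 8 g. Nor does the protocol explain how 8 g was chosen. It is 8/14 = 57% of the fall seen in the earlier spironolactone study, so it is not that effect carried over.
- **That a within-arm fall would be reported as the treatment effect.** The endpoint wording permits this reading, but the analysis paragraph points the other way.

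On the schedule, it is fair to reply that few participants are likely to be randomised at week 6, and that the extension comes before randomisation and so cannot favour either arm. Visit windows may also sit in the full protocol. But the article states two fixed durations that conflict under its own Table 2, which is a contradiction and not an omission.

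Adjustment for baseline can be called a preference. It is an improvement to the planned unpaired t-test, and the wording correction does not depend on it.

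**Conclusion.** The point holds as a mislabelled primary endpoint together with a schedule contradiction in a small subgroup. The trial estimates 36 weeks of continuing sevelamer versus switching to placebo, after 4 weeks of shared exposure, in run-in completers. It does not estimate 40 weeks of sevelamer versus none. For week-6 randomisations the stated durations imply either 34 blinded weeks or a week-42 final visit.

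Neither part biases the arm comparison, and neither changes the stated power, which stays at about 79% to 80% with 55 per arm when the 8 g is taken as the plan words it. That the subgroup is small is an expectation drawn from the phosphate figures, since the protocol gives no count. The consequence is for interpretation: the conclusion must be narrower than the endpoint wording suggests.

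**What to change.** 1. Restate the primary endpoint as the between-arm difference in left ventricular mass at the final visit, adjusted for the pre-run-in value. That value is already collected. With a linear adjustment, the residual variance is in large samples no greater than that of the change score, so precision should not suffer.
2. Describe the contrast, in the endpoint and in the hypothesis, as randomised continuation of sevelamer versus switch to placebo after a 4-week (up to 6-week) open-label run-in, in participants who completed it.
3. Reconcile Table 2 with Randomisation and Treatment Phase, so that the final visit has one stated anchor, either baseline or randomisation, that also covers week-6 randomisations. The sponsor should choose the anchor.
4. State that the 8 g refers to this between-arm contrast.

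The cost is wording in the protocol and analysis plan, plus one covariate in the primary model. No extra scan, visit or participant is needed. The downside is a slightly narrower claim.

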### Baseline Studies

All subjects will undergo a baseline visit (Figure 1) during which the following will be performed: i) questionnaire regarding past medical history, drug history and tobacco and alcohol consumption; ii) clinical examination of all systems; iii) measurement of height, weight, hips and waist; iv) 12-lead electrocardiogram (ECG); v) office brachial blood pressure and heart rate measurement in triplicate using the non-dominant arm following 15 minutes of rest with a validated oscillometric sphygmomanometer (HEM-705CP, Omron, Henfield, United Kingdom[17] or Dinamap Procare 200, GE Healthcare, United Kingdom[18]) according to British Hypertension Society guidelines[19]; vi) applanation tonometry to determine carotid-femoral aortic pulse wave velocity; vii) applanation tonometry to derive central pressure waveforms from pulse wave analysis and to determine central systolic and diastolic pressures and augmentation index; viii) dual energy x-ray absorptiometry (DEXA) scanning to assess bone mineral density as recommended by the World Health Organisation[20,21]; ix) collection of serum and plasma following 30 minutes of supine rest for haematological and biochemical analysis including serum calcium, phosphate, 1,25-dihydroxyvitamin D and parathyroid hormone (PTH); x) storage of serum and plasma at -80°C for future assay of biomarkers associated with cardiovascular function and calcification; xi) collection of a spot urine sample to determine albumin: creatinine ratio; xii) storage of a spot urine sample at -80°C for future proteomic studies; xiii) transthoracic echocardiography to determine systolic and diastolic ventricular function and measures of ventricular-vascular interaction; xiv) a lateral plain abdominal radiograph to semi-quantitatively assess abdominal aortic calcification as previously described[22]; xv) cardiac magnetic resonance imaging (CMR) to determine ventricular volumes, function and mass and aortic distensibility as previously described[23]; xvi) 24-hour urine collection for determination of phosphate excretion; and xvii) 24-hour ambulatory blood pressure and heart rate monitoring with a validated ambulatory blood pressure monitor (ABPM-04, Meditech, Budapest, Hungary) [24]. Eligible female subjects of childbearing age will undergo urine pregnancy testing prior to entry into the study.

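### Pulse wave measures are taken twice before randomisation, but the planned comparison adjusts for neither value and gives the second no stated role, so precision is lost on a secondary endpoint

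*Protocol article*

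**What the plan says.** Under Baseline Studies, the week-0 visit includes "applanation tonometry to determine carotid-femoral aortic pulse wave velocity" and "applanation tonometry to derive central pressure waveforms from pulse wave analysis and to determine central systolic and diastolic pressures and augmentation index". Run-in comes next: "Following baseline studies all subjects will receive 1600 mg of sevelamer carbonate with meals for 4 weeks during an open-label run-in phase".

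Under Randomisation and Treatment Phase, a further attendance is set: "At the end of the open-label run-in phase subjects will attend for a second study visit and the following will be repeated". The list that follows includes "applanation tonometry to determine aortic pulse wave velocity" and pulse wave analysis, but no cardiac magnetic resonance imaging (CMR). Only then does allocation take place: "Participants will then be randomised by computer assignment to continue 1600 mg (or half-dose) sevelamer with meals or receive an identical placebo". The final visit is 40 weeks after the baseline studies.

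Under Endpoints, the secondary endpoint is "change in arterial stiffness as assessed using pulse wave velocity and pulse wave analysis". Under Planned Statistical Analysis: "Comparisons will be performed between the groups at baseline and after the 36-week treatment phase". For normally distributed variables, that section names unpaired t-tests, chi-squared tests or repeated measures analysis of variance. It names no baseline-adjusted model for the comparison between arms and does not say how the end-of-run-in pulse wave values are used.

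**The concern.** Each subject who reaches randomisation is due to have two pulse wave measurements that allocation cannot have influenced. Both can serve as covariates, and together they should predict the week-40 value better than either does alone. An unpaired t-test on change from week 0 uses one of them, with its coefficient fixed at one, and ignores the other.

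What is at stake is the width of the confidence interval for arterial stiffness. The Background proposes stiffness as the route by which phosphate acts on the heart, and the Hypothesis includes it. The sample size was set for left ventricular mass alone, so nothing in the plan secures precision for the pulse wave measures. Information already scheduled for collection should be used.

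**Working it through.** **The plan's own figure.** No standard deviation, correlation or power is given for any pulse wave measure. The only sample-size figure is for left ventricular mass: 55 per arm for 8 g, SD 15 g, two-sided 5%, 80% power. The normal approximation gives 2 × (1.960 + 0.842)² × 15² / 8² = 55.2, rounded up to 56, and power at 55 per arm is 79.9%. The stated figure is reproduced to within one subject per arm. It has no bearing on this point.

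**Assumptions.** Variance is equal at all visits and scaled to 1. Let r be the correlation of each pre-randomisation value with the week-40 value, taken as 0.5 to 0.8. Let r₁₂ be the correlation between the two pre-randomisation values. It is taken first as equal to r, then as r + 0.1, because those visits are only about four weeks apart. None of these values comes from the documents.

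**Formulas** (residual variance, to which the variance of the treatment effect is proportional):
- A, simple change from week 0: 2(1 − r)
- B, final value adjusted for week 0: 1 − r²
- C, final value adjusted for the mean of both pre-randomisation values: 1 − 2r²/(1 + r₁₂)

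At r = r₁₂ = 0.7:
- A = 2 × 0.3 = 0.600
- B = 1 − 0.49 = 0.510
- C = 1 − 0.98/1.7 = 0.424

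| r | r₁₂ | A | B | C | Cut, B to C | Cut, A to C |
|---|---|---|---|---|---|---|
| 0.5 | 0.5 | 1.000 | 0.750 | 0.667 | 11% | 33% |
| 0.6 | 0.6 | 0.800 | 0.640 | 0.550 | 14% | 31% |
| 0.7 | 0.7 | 0.600 | 0.510 | 0.424 | 17% | 29% |
| 0.8 | 0.8 | 0.400 | 0.360 | 0.289 | 20% | 28% |
| 0.5 | 0.6 | 1.000 | 0.750 | 0.688 | 8% | 31% |
| 0.6 | 0.7 | 0.800 | 0.640 | 0.576 | 10% | 28% |
| 0.7 | 0.8 | 0.600 | 0.510 | 0.456 | 11% | 24% |
| 0.8 | 0.9 | 0.400 | 0.360 | 0.326 | 9% | 18% |

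**Splitting the gain.** The second measurement accounts for the step from B to C, 8–20%. The step from A to B is ordinary adjustment for week 0. Since B/A = (1 + r)/2, that step is worth 25%, 20%, 15% and 10% at r = 0.5, 0.6, 0.7 and 0.8. The 28–33% total therefore combines two gains, and it falls to 18–31% when the two early visits are more alike.

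**On the interval.** Width scales with the square root of variance. From B to C it shrinks by 1 − √0.917 = 4% at the low end and 1 − √0.802 = 10% at the high end.

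**Bias.** Both values precede allocation, so their expected values are the same in the two arms. Four weeks of open-label sevelamer may shift the second value, but it does so in both arms alike. Change from week 0, change from the randomisation visit and the adjusted final value all have the same expected difference between arms.

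**The case against.** The strongest reply is that nothing here is an error. A t-test on change from week 0 is valid and unbiased. The end-of-run-in measurement has an evident descriptive purpose, since run-in is meant to assess efficacy and tolerability, and a trial need not use every measurement as a covariate. Repeated measures analysis of variance could include all three visits. Covariate choice for a secondary endpoint is also often left to a statistical analysis plan, which is not shown here.

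Much of this stands, and it is why the point is minor. Three things remain. The article does specify the methods for comparing the groups, and none of them is baseline-adjusted. The section does not say which visits enter a repeated measures analysis. Such an analysis would also treat a pre-randomisation value as an outcome: with the best contrast, change from the mean of both values, the variance at r = r₁₂ = 0.7 is 1 + (1 + 0.7)/2 − 1.4 = 0.450, still above 0.424. The stepwise regression models listed for vascular stiffness do not fill the gap, because they are not described as the treatment comparison and do not name the pre-randomisation values as fixed covariates.

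A reader might go further and infer that the endpoint is tied to neither visit, so that two rival change scores exist and picking the significant one raises the type I error from 5% to 8–9%. The documents do not support that. The article uses baseline for week 0 and calls the end-of-run-in attendance a second study visit. The phrase about the end of the 36-week phase names a time point, week 4 + 36 = 40, and does not define an interval starting at randomisation. No section proposes a change from the randomisation visit or a choice between the two.

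**Conclusion.** The concern holds as a minor point about efficiency. The planned comparison of pulse wave measures is unbiased but less precise than the scheduled data allow. With correlations of 0.5 to 0.8, the second pre-randomisation value is worth about 8–20% of the variance beyond single-baseline adjustment. Against a simple change score the cut is about 28–33% if all visits are equally correlated. It would be wrong to credit that larger figure to the second measurement alone. These sizes rest on assumed correlations and equal variances. The direction does not depend on the exact values: under the equal-variance and exchangeable assumptions used here, C is below B whenever r₁₂ is below 1.

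The primary endpoint is unaffected, because CMR is not repeated at the end of run-in and left ventricular mass by CMR has only one pre-randomisation value. An analysis plan that is not shown may already specify the adjustment. If so, the article's wording only needs to be brought into line with it.

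**What to change.** For pulse wave velocity, heart-rate-corrected augmentation index (AIx75) and central pressures, state that the between-arm difference in the final-visit value will be estimated by a linear model adjusted for both pre-randomisation values, entered either as two covariates or as their mean. Choose one form in advance. State that this is the single inferential analysis for these measures, and that changes from week 0 or from the randomisation visit will be reported descriptively only.

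The cost is a few lines of analysis text. Both measurements are already scheduled, so no visits, patients or procedures are added. With 55 analysed per arm, the residual degrees of freedom fall from 108 to 107 with the mean as covariate, or to 106 with two covariates, which is negligible.
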